**Additional file 1**

**Work Packages 1-8**

# WP 1: Effectiveness of a structured intervention for improving motor skills in Danish preschool children. A randomised controlled trial.

## Background

There are reports of randomised controlled trials indicating that children’s motor skills can be improved through interventions in preschool, but the study populations have been small, the intervention periods short (<12 weeks), and the follow-up periods less than half a year(1). Thus, there is an urgent need for high quality studies involving larger samples and longer intervention and follow-up periods (see main body of the protocol).

Besides the importance of a child´s actual fundamental movement skills, perceived motor competence seems to be important in supporting physically active behaviour, and it is thought to be a key motivational factor in supporting engagement in physical activities and sports(2-4). Perceived motor competence is defined as children´s self-perceptions about their capabilities in physical or motor domains (5, 6). Although children have unrealistic perceptions of actual competence during their early years, Stodden and colleagues argue that a perceived high level of motor skills might be one of the reasons to engage in physical activities during the early childhood years. The hypothesis is that children with low perceptions of competence find physical activity less enjoyable than their peers with higher perceptions of competence and thus are less likely to be physically active and may be drawn into a negative spiral of disengagement (2).

Furthermore, children with high perceptions of competence are likely to select challenging tasks, enjoy the learning process, exhibit higher self-esteem, exert greater effort to master skills, and persist in the face of difficulty (3, 7).

### Objectives

The primary objective of this work package is to determine the effectiveness of an adaptable but structured intervention to improve motor skills and perceived motor competence in preschool children.

### Intervention

See main protocol and Appendix 2.

### Variables

*Primary outcome:*

Motor skills as assessed by the MovementABC-2 (as described in the main protocol) at the 18 month follow-up (spring 2018). At this point, the children will have received the intervention for 12 months after a six months phase-in period.

*Secondary outcomes:*

Child’s perceived physical competence

The perceived motor competence relating to everyday activities will be measured by the Perceived Physical Competence (PPC) subscale of Harter and Pike’s Pictorial Scale of Perceived Competence and Social Acceptance (PSPCSA) for preschool- and kindergarten-age children (4 to 7 years)(5). The PPC subscale assesses the children’s self-perceptions related to their ability to run, hop, swing, climb, tie shoelaces, and skip. On each pictorial plate, two pictures will be displayed side by side; one picture depicts a child who is competent in a particular task, and the other depicts a child who is not competent. The child selects the picture that is most like him/herself. Then, the child focuses on the selected picture and indicates whether

(s)he is ‘‘a little bit like’’ the child in the picture or ‘‘a lot like’’ the child in the picture. The range of scores for each item on the subscale is 1 (low competence) to 4 (high competence). The instrument has an internal consistency for the individual PPC subscale for preschool children of 0.62 (5). The assessment of the PPC subscale takes around 5 minutes.

Parent-perceived motor competence

The rating of parents’ perception of their child’s athletic coordination compared to other children of the same age has often been related to preschool-age children´s actual physical activity (9-11). An often used question for this assessment is “Compared with other children of the same age and sex, how would you describe your child’s level of athletic coordination?” with a response on a 5-point Likert scale, from 1 (much less coordinated) to 5 (much more coordinated) (10, 11). This question will be included in the parental baseline questionnaire and also mailed to the parents at the time of the last follow up before the child leaves preschool.

## Length of follow up

The duration of the follow up is 6 to 30 months, which covers the period from the beginning of the intervention until the last measurement before the child leaves preschool (see Figure 1 in the main protocol).

## Analyses of effect

Simple univariate statistics will be used to describe the outcomes and covariates by preschool. Bivariate analysis adjusted for the design effect will be done to determine if there were any imbalances in the baseline covariates among the two groups.

Multilevel linear regression models will be constructed to assess the effectiveness of the intervention on motor skill performance. The baseline value of the outcome variable, time since baseline, intervention group and any imbalanced covariates will be added to the model along with preschool and socioeconomic status of the area as random effects. The interaction between preschool and intervention group will be tested. The assumptions for the models will be checked.

Multilevel ordinal regression models will be constructed to assess the effectiveness of the intervention on the parents’ perception of their child’s motor competence. The baseline value of the parents’ perception, time since baseline, intervention group and imbalanced covariates will be independent variables. The school and socioeconomic status of the area will be entered as random effects and the interaction between school and intervention will be tested. The model’s assumptions will be tested.

The above analyses will be repeated on a subsample of children who were considered to have a ‘poor’ level of motor competence at baseline.

An analysis will be conducted to determine if the children who dropped out of the study were different from those who remained, based on the baseline values of the outcome variables and the covariates.

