### Covariates

The following covariates will be accounted for when analysing the results: sex, age, socioeconomic status, child well-being and parental MSK health.

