### Analyses

Multilevel logistic regression will be conducted to determine if there was a difference in aberrant movement problems by intervention group after adjusting for time in intervention, imbalanced covariates from WP1, school and socioeconomic status of the school.

Multilevel Poisson regression will be conducted if the number of MSK diagnoses of persistent problems differs by intervention group after adjusting for time on intervention, imbalanced covariates from WP1, school and socioeconomic status of the school.

The age-specific, sex-specific and age- and sex-specific incidence rate of MSK conditions will be calculated.

Longitudinal latent class analysis and latent class growth analysis will be conducted to describe the MSK developmental patterns. The sequential model comparisons (T classes vs. T + 1 classes) and chi-square goodness-of-fit test will be evaluated using the parametric bootstrapping technique. Lastly, the associations between class membership and the prevalence of related measures will be examined using a confirmatory latent class analysis approach.

Multilevel longitudinal logistic regression analyses will be conducted to determine if poor motor performance is associated with aberrant movement patterns after adjusting for age, sex and other important covariates. The interaction between time and poor motor performance will be examined.

Multilevel longitudinal Poisson regression analyses will be conducted to determine if motor performance at the end of preschool is predictive of the number of MSK diagnoses throughout the school years after adjusting for age, sex and other important covariates. The interaction between time and motor performance will be examined.

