### Analyses

For the RCT study, multilevel linear regression models will be constructed to assess the effectiveness of the intervention on psychological wellbeing. The baseline value of the outcome variable, time since baseline, intervention group and any imbalanced covariates will be added to the model along with preschool and socioeconomic status of the area as random effects. The interaction between preschool and intervention group will be tested. The assumptions for the models will be checked. Similar multilevel linear regression models will be constructed for both the child’s physical and emotional wellbeing and self-esteem. Measures for both groups at baseline and at following points of data collection will be further analyzed using linear mixed effects models (random coefficient models and multilevel models).

The above analyses will be repeated on the children who were considered to have a ‘poor’ level of motor skills at baseline.

In addition to the WP1 analysis of the covariates, an analysis will be conducted to determine if the children who dropped out of the study were different from those who remained, based on the baseline values of the outcome variables.

For the cohort study, longitudinal latent class analysis and latent class growth analysis will be conducted to describe the developmental patterns of wellbeing.

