### Analyses

Simple univariate statistics will be calculated to describe the outcomes and covariates by school.

Multilevel linear regression models will be constructed to assess the effectiveness of the intervention on executive functioning. The baseline value of the outcome variable, time since baseline, intervention group and the covariates of sex, age, estimated general intelligence, socioeconomic status of the household and child well-being at baseline will be added to the model along with school and socioeconomic status of the area as random effects. The interaction between school and intervention group will be tested. The assumptions for the models will be checked.

Similarly multilevel linear regression models will be constructed to assess the effectiveness of the intervention on academic performance as measured by the Grade 9 examination grades. The baseline value of the outcome variable, time since baseline, intervention group and the covariates of sex, age, estimated general intelligence, socioeconomic status of the household and child well-being at baseline will be added to the model along with school and socioeconomic status of the area as random effects. The interaction between school and intervention group will be tested. The assumptions for the models will be checked.

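### Observed baseline imbalance decides which covariates enter the between-arm models of WP 1, 3, 4 and 6, so age and sex would usually be left out, at a modest cost in precision

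*Protocol*

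**What the plan says.** In WP 1 (Analyses of effect) the arms are compared at baseline: "Bivariate analysis adjusted for the design effect will be done to determine if there were any imbalances in the baseline covariates among the two groups". No threshold and no list of candidate covariates is given. The result feeds the primary linear model: "The baseline value of the outcome variable, time since baseline, intervention group and any imbalanced covariates will be added to the model". The ordinal model for the parents' rating follows suit: "The baseline value of the parents’ perception, time since baseline, intervention group and imbalanced covariates will be independent variables". The terms always in the linear model are therefore baseline outcome, time since baseline, arm and, as random terms, preschool and area socioeconomic status (SES). Age and sex are not named.

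The rule recurs elsewhere:
- **WP 3 (Analyses):** both between-arm models adjust for "imbalanced covariates from WP1".
- **WP 4 (Analysis plan):** the comparison of changes in activity and adiposity adjusts for baseline outcome and for covariates found imbalanced.
- **WP 6 (Analyses):** "intervention group and any imbalanced covariates will be added to the model".

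Two of these work packages also carry a separate list. WP 3 (Covariates) says: "The following covariates will be accounted for when analysing the results: sex, age, socioeconomic status, child well-being and parental MSK health". WP 6 (Covariates) similarly names sex, age, SES, estimated intelligence, executive function and early developmental difficulties. WP 7 (Analyses) works differently, with a model that contains "intervention group and the covariates of sex, age, estimated general intelligence, socioeconomic status of the household and child well-being at baseline", whatever the balance.

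**The concern.** A covariate is worth adjusting for because it predicts the outcome. Under sound randomisation an arm difference at baseline is chance, and its size says nothing about prognostic value. A rule that admits covariates on imbalance will usually leave strong predictors out and will sometimes let irrelevant ones in. It also means that the primary model is not known until the baseline data have been compared by arm.

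Age and sex are the obvious predictors here. WP 4 sets out to produce motor-skill reference data and percentile curves by age and sex, so the document itself expects motor skill to vary with both. Precision matters for how the result will be used: WP 1 (Perspectives) says that failure to show an improvement should probably end further funding of such programmes.

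**Working it through.** The document gives no sample size, power, ICC or imbalance threshold for WP 1, so there is no stated figure to reproduce. Everything below rests on labelled assumptions.

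**1. How often age and sex are omitted.** Assume sound randomisation, independent comparisons and flagging at level a. Then P(both omitted) = (1 − a)².
- a = 0.05: 0.95² = 0.90
- a = 0.10: 0.90² = 0.81
- a = 0.20: 0.80² = 0.64

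**2. How open the model is.** With k independent candidates at a = 0.05, the chance that at least one is flagged by luck is 1 − 0.95^k, which is 0.23 for k = 5 and 0.40 for k = 10. Five candidates allow 2⁵ = 32 possible models.

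**3. Type I error.** Cluster means were simulated under the null, with one covariate, 10 or 20 clusters per arm, flagging at p < 0.05 and 40,000 runs per setting.

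| Correlation of covariate with outcome | Adjust only if flagged (10; 20 clusters per arm) |
|---|---|
| 0.3 | 0.047; 0.049 |
| 0.5 | 0.044; 0.045 |
| 0.7 | 0.035; 0.038 |

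Always adjusting gave 0.048 to 0.051. The selective rule is at or below the nominal 0.05, so it is conservative.

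**4. Loss of precision.** Let the omitted covariates explain a share R² of child-level residual variance, with ICC ρ and m children per preschool. The treatment-effect variance is inflated by

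[ρ + (1 − ρ)/m] / [ρ + (1 − ρ)(1 − R²)/m].

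- **Upper bound (ρ = 0):** the ratio is 1/(1 − R²). This gives 1/0.95 = 1.05 at R² = 0.05 and 1/0.80 = 1.25 at R² = 0.20.
- **ρ = 0.05, m = 20:** (1 − ρ)/m = 0.95/20 = 0.0475.
  - R² = 0.05: 0.0975/(0.05 + 0.0451) = 1.025
  - R² = 0.20: 0.0975/(0.05 + 0.0380) = 1.108

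**5. The same in power.** Take 80% power with adjustment and a two-sided 5% test. Without adjustment, power = Φ((1.960 + 0.842)/√ratio − 1.960).
- Upper bound: ratio 1.05 gives 78% and ratio 1.25 gives 71%.
- ρ = 0.05, m = 20: ratio 1.025 gives Φ(0.81) = 79% and ratio 1.108 gives Φ(0.70) = 76%.

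**The case against.** **An analysis plan could settle the covariates.** It could, but the protocol does not leave the matter open. It states a selection rule. A plan that followed it would keep the fault, and one that dropped it would depart from the protocol.

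**No test is named.** This is true: no p-value or cut-off appears. Adjusting for the design effect points to an inferential comparison, but the 0.90 depends on the assumed 5%. The model depends on the data under any criterion.

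**Baseline comparison may be informative.** If children were recruited after their preschool was allocated, the arms could differ systematically. The text at hand does not describe recruitment order, so this cannot be excluded. It would justify looking at balance and running a sensitivity analysis. It would not justify leaving out known predictors that happen to look balanced.

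**Age may add little.** The baseline outcome is always in the model and may carry part of the age effect. MABC-2 scoring is left to the main protocol, and if the score is age-standardised the gain from age shrinks. This stands and limits the size of the point.

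**Stronger readings that the documents do not support.**
- A reader might infer that choosing covariates this way inflates the type I error. The simulation shows the opposite direction.
- A reader might take 25% as the expected loss of precision. That is the inflation of child-level residual variance at R² = 0.20. It carries over to the treatment effect only if there is no between-preschool variance.
- A reader might call the WP 3 and WP 6 lists a flat contradiction of their models. Both work packages also have cohort objectives, and WP 3's motor-performance cohort models do adjust for age and sex. The lists may belong to the cohort analyses, or may add to the imbalance rule. This is an ambiguity to resolve.

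**Conclusion.** The point holds as a fault in a stated rule. The primary model and the between-arm models of WP 3, WP 4 and WP 6 take covariates on observed imbalance, and age and sex would usually be absent. The consequences are a model choice made after seeing data and a modest loss of precision: at most 5% to 25% in treatment-effect variance, and about 2.5% to 11% at ICC 0.05 with 20 children per preschool.

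These figures assume R² of 5% to 20% at child level and that the covariates explain no larger share of the between-preschool variance. The existence of the rule is certain. The size of the loss is not, because scoring, cluster numbers and ICC are not in the text at hand. The change is worth making because WP 7 already follows the better approach within the same trial.

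**What to change.** 1. In WP 1, WP 3, WP 4 and WP 6, replace the adjustment for imbalanced covariates with a pre-specified list used whatever the observed balance: baseline outcome, age, sex and any factor used to stratify the randomisation. Keep area or school SES as each model already has it.
2. In WP 3 and WP 6, reconcile the between-arm models with the covariates that each work package says it will account for. State whether those lists apply to the RCT models, the cohort models or both. Do not drop any named covariate silently.
3. In the between-arm models use baseline values only. This matters for the WP 6 item on developmental difficulties, because the WP 8 definition of early developmental risk admits information arising during the project period.
4. Present baseline data by arm descriptively, and use any observed imbalance only for a sensitivity analysis.

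The cost is small. WP 1 and WP 4 need about a sentence each. WP 3 and WP 6 need somewhat more, because their lists must be assigned to particular models. Age and sex are already named as covariates in WP 3, WP 6 and WP 7, so no new data collection should be needed.

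### WP 1 fixes its primary outcome at 18 months, but the motor-skill model it writes out is not tied to that visit

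*Protocol*

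**What the plan says.** Under Variables, WP 1 gives the primary outcome as "Motor skills as assessed by the MovementABC-2 (as described in the main protocol) at the 18 month follow-up (spring 2018"), and describes the exposure by that visit: "the children will have received the intervention for 12 months after a six months phase-in period". Under Length of follow up it states "The duration of the follow up is 6 to 30 months", counted up to each child's final preschool assessment.

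Under Analyses of effect, multilevel linear regression is planned for motor skills. Of the fixed terms it says: "The baseline value of the outcome variable, time since baseline, intervention group and any imbalanced covariates will be added to the model". Preschool and the area's socioeconomic status are the random effects. Only one interaction is named: "The interaction between preschool and intervention group will be tested". The section does not mention 18 months, does not say which visits supply records, and lists neither a group-by-time term nor a random effect for the child.

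The ordinal model for the parents' rating, in the same section, has the same structure, time since baseline included. By the Variables section, that rating is collected at baseline and at the last follow-up before the child leaves preschool.

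**The concern.** An endpoint at one visit calls for a group contrast at that visit. The written model carries a time term and a single group coefficient, beside a follow-up that differs between children. That structure suits variable follow-up better than a single 18-month measurement, and in the sister model for the parents' rating it does serve variable follow-up. An analyst could therefore put in 18-month records, each child's last record, or all records, and cite the protocol for any of the three.

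The choice affects the answer. The Variables section itself separates a six-month phase-in from the 12 months of intervention, so a weaker effect at an early visit is plausible. Averaging that visit in could pull the coefficient below the 18-month effect. WP 1's Perspectives section says that, if no improvement can be shown, further resources for such programmes should probably stop, so attenuation of the main estimate would bear on a stated decision.

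**Working it through.** The document gives no sample size, power, effect size or variance, so there is no planned figure to reproduce. The check is what a single group coefficient estimates, as a multiple of the 18-month effect d.

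**Inputs from the protocol.** Primary visit 18 months; follow-up 6 to 30 months; one group term with additive time (WP 1). Motor skills are obtained annually (WP 4, analysis plan).

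**Assumptions.** MABC-2 visits at 6, 18 and 30 months (the schedule figure is in the main protocol, which is not shown); the two groups have equal numbers at each visit; five illustrative effect paths; where children leave, one third do so after each visit.

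**Formula.** With effects e6, e18 = d and e30, and visit weights w, the group coefficient is

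(w6·e6 + w18·d + w30·e30) / (w6 + w18 + w30).

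**Weights.**
- A. All visits, nobody leaves: 1:1:1.
- B. All visits, children leave as assumed: 3:2:1.
- C. As B, with a child-level correlation of 0.6 fitted. A child with m visits gives each visit weight 1/(1 + 0.6(m − 1)), which is 1, 0.625 and 0.4545 for m = 1, 2, 3. The visit weights are 1 + 0.625 + 0.4545 = 2.0795, then 0.625 + 0.4545 = 1.0795, then 0.4545; they sum to 3.6136 before rounding.
- D. Last visit only, equal thirds: 1:1:1.
- E. 18-month records only: 0:1:0.

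**Examples for the path 0, d, d.**
- A and D: (0 + d + d)/3 = 0.67 d.
- B: (0 + 2d + d)/6 = 0.50 d.
- C: (1.0795 + 0.4545)d/3.6136 = 0.425 d.
- E: d.

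| Effect at 6, 18, 30 months | A | B | C | D | E |
|---|---|---|---|---|---|
| 0, d, d | 0.67 | 0.50 | 0.425 | 0.67 | 1.00 |
| 0.5d, d, d | 0.83 | 0.75 | 0.71 | 0.83 | 1.00 |
| 0, d, 2d | 1.00 | 0.67 | 0.55 | 1.00 | 1.00 |
| d/3, d, 5d/3 | 1.00 | 0.78 | 0.70 | 1.00 | 1.00 |
| d, d, d | 1.00 | 1.00 | 1.00 | 1.00 | 1.00 |

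Column C needs a child effect that the text does not list. For the model as written the lowest value is 0.50 (column B).

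The table is not a bound. With equal weights the coefficient is d + (e6 + e30 − 2d)/3, so it exceeds d if the effect grows more after 18 months than between 6 and 18.

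**Covariance.** If all visits enter and the only random effects are preschool and area socioeconomic status, repeated visits of one child are treated as independent within the preschool. The document gives no correlation from which to size the effect on the standard error, and under one record per child the point does not arise.

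**The case against.** The best reply is that the plan already means 18-month records. The Variables section defines the outcome at 18 months, Analyses of effect models the outcome variable, and time since baseline then only adjusts for differing test dates. Other work packages support one record per child. WP 6 uses the same model sentence and then adds a separate mixed-model analysis of the repeated measures. WP 3 says longitudinal and names a time interaction when it wants one. The missing child effect points the same way. The 6-to-30-month range may simply describe follow-up, including the later parents' rating.

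Much of this stands. The protocol never says that visits are pooled, and on the 18-month reading the coefficient is the 18-month effect in children still in preschool. A reader might infer that the model cannot estimate the 18-month effect on any reading; the text does not support that.

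The reply does not close the gap, because one record per child need not be the 18-month record. The parents' rating has the same model structure and uses the last visit.

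A reader might also infer a definite loss of power, a known share of children without a primary outcome by design, or the same fault in WP 6. The document gives no power, sample size or year-group sizes, and eligibility and schedule are in the main protocol. For the RCT, WP 6 fixes no 18-month primary visit and already adds a repeated-measures model.

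**Conclusion.** The point holds as a mismatch between a stated endpoint and a stated model. The primary outcome is at 18 months, and the model written for it does not say that its group term is the 18-month contrast. If records from several visits or each child's last visit enter, the coefficient is generally a different quantity, about 0.425 to 1.00 times the 18-month effect over the cases tried. That range rests on assumed visits, effect paths and leaving pattern, and it is conditional on pooling or last-visit use, which the text neither states nor rules out. With 18-month records only, the discrepancy is zero.

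This is a low-cost improvement to the primary analysis, not an error that invalidates it. A separate SAP, not shown, may already settle the matter.

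**What to change.** State in WP 1, Analyses of effect, that the primary analysis is the group contrast in MABC-2 at the 18-month visit. Either of two forms will do:

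- a model on 18-month records only, adjusted for the baseline score, with preschool as a random effect; or
- a mixed model on all visits with visit as a category, group-by-visit terms, the baseline score and random intercepts for preschool and child, reading off the 18-month contrast.

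Label contrasts at other visits as secondary. Settle the wording before outcome data are seen.

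The cost is a few lines of text and no new data. The 18-month contrast will have a somewhat wider interval than a coefficient pooled over visits.

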## Perspectives

The Svendborg City Council has granted generous resources to educate the staff; the staff at the preschools is eager to participate; the preschool teachers have contributed to the design of the intervention, ensuring a sense of ownership and involvement; and there is experience with conducting large, cluster randomised controlled trials in the Municipality. Therefore, the conditions for implementation of the intervention in the preschools are optimal. Consequently, if we cannot show an improvement in the children’s motor skills using this framework, further allocation of resources to programs to improve motor development in preschools should probably be discontinued.

On the other hand, if the intervention does succeed, the program can easily be applied in other Danish municipalities due to the design, where each preschool applies the intervention principles in a way to suit their individual conditions regarding physical environment, staffing, etc.

Finally, if the intervention improves motor competence in the children with the highest need for improvement, targeted interventions could be considered if, in some settings, prioritizing of resources is necessary.

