# WP 6: Association between motor skills and wellbeing

**Background**

Motor skills contribute to children’s physical, cognitive and social development [1]. However, the relationship between motor skills and wellbeing has been less investigated, with most studies focusing on the relationship between poor motor skills and wellbeing [2]. Poor motor skills have been associated with fewer playmates, fewer spare-time activities, less time spent engaged in social activities and symptoms of anxiety and depression [2]. Motor skills are further seen as an important foundation for participation in physical activities [3] and level of physical activity [1], which has been linked to mental health, wellbeing and fewer emotional and social problems [2-5]. Studies of physical activity or exercise programs indicate improvements in mood, prevention of depression and reduction in depression and anxiety symptoms [4]. The importance of regular motor skills training in preschool children in terms of wellbeing has, to our knowledge, not been investigated previously. In general, there is a need for studies with large sample sizes that follow development for a longer period of time in order to investigate both the short-term and the potential long-term effects of a motor skills intervention on child wellbeing from a developmental perspective [2,4].

Wellbeing is a multi-faceted concept involving physical, psychological, cognitive, social and economic domains. Wellbeing is influenced not just by contextual and individual factors in these domains but also the child’s perception of these factors [5,6]. The motor skills intervention as described in the main body of the application is directed towards improvement in motor skills, but as the intervention is integrated with the preschool curriculum, the intervention may also influence peer interactions and staff-child interactions, both in the introduced motor skills activities and in other more familiar activities. Similarly, the children may experience new opportunities for participation in activities in preschool with the possibility of changes in self-perception.

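### The preschool-by-intervention interaction planned in WP1, WP6 and the WP7 executive-function model cannot be tested as such if whole preschools are allocated; the arm effect itself is not harmed

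*Protocol*

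**What the plan says.** All places are in the Protocol (Additional file 1).

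- **WP 1, Analyses of effect, linear model for motor skills (primary outcome).** Intervention group is fitted with "preschool and socioeconomic status of the area as random effects", and then: "The interaction between preschool and intervention group will be tested".
- **WP 1, Analyses of effect, ordinal model for the parents' perception.** "The school and socioeconomic status of the area will be entered as random effects and the interaction between school and intervention will be tested".
- **WP 6, Analyses.** The linear model has the same random effects and the same interaction test. Similar models follow for physical and emotional wellbeing and for self-esteem.
- **WP 7, Analyses.** The executive-function model and the Grade 9 model both use "school and socioeconomic status of the area as random effects", and each adds: "The interaction between school and intervention group will be tested".

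WP 1 and WP 6 repeat their analyses in children with poor motor skills at baseline. WP 8 repeats the other packages' analyses in children at developmental risk. The interaction test goes with them.

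The unit of randomisation is not stated; the design is referred to a main protocol that is not part of this document. The indications are:

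- WP 1, Analyses of effect, corrects the baseline comparison of the two groups for clustering.
- WP 1, Perspectives, lists among the favourable conditions that "there is experience with conducting large, cluster randomised controlled trials in the Municipality", and describes each preschool as adapting the programme to its own circumstances.
- WP 6, Background, expects wider effects on staff and peers "as the intervention is integrated with the preschool curriculum".

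Nothing in the document describes a preschool with children in both arms, or one that changes arm.

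**The concern.** An interaction between preschool and arm asks whether the intervention effect differs from one preschool to another. To answer it, the effect must be observable within preschools, which requires intervention and control children in the same preschool. If preschools are allocated whole, no such contrast exists.

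The analyst would then have three courses: depart from the protocol, fit a model whose parameters are not identified, or fit a restricted model and report ordinary variation between preschools as variation in effect. The last is the one to guard against. Each preschool adapts the programme in its own way, so a reader will want to know whether the effect varies, and could take the result as an answer.

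**Working it through.** The document gives no number of preschools, intraclass correlation or sample size on this point, so there is no figure to reproduce. The check is of estimability. The numbers of preschools and children below are assumptions, used only to show that the result does not depend on them.

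**1. Interaction as fixed terms.** Let there be *K* preschools, each in one arm. The interaction column for a preschool is its indicator multiplied by the arm indicator. For an intervention preschool this equals the preschool's own indicator; for a control preschool it is a column of zeros. Neither adds anything to a model that already holds the preschool indicators. Ranks of the design matrix, the same with 10 or 30 children per preschool:

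| *K* (assumed) | Nested in arm: arm + preschool | Nested: + interaction | Crossed with arm: arm + preschool | Crossed: + interaction |
|---|---|---|---|---|
| 10 | 10 | 10 | 11 | 20 |
| 20 | 20 | 20 | 21 | 40 |
| 40 | 40 | 40 | 41 | 80 |

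Nested, the interaction has 10 − 10 = 20 − 20 = 40 − 40 = 0 degrees of freedom. Crossed, shown for contrast, it has *K* − 1: 20 − 11 = 9, 40 − 21 = 19 and 80 − 41 = 39.

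**2. Interaction as a random arm slope.** Let the preschool intercept have variance t0, the arm slope variance t1, and their covariance t01. With one arm per preschool, the data show only

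- control preschools: between-preschool variance = t0
- intervention preschools: between-preschool variance = t0 + 2·t01 + t1

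Three parameters therefore rest on two observable quantities. Different values cannot be told apart:

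| t0 | t01 | t1 | Control | Intervention |
|---|---|---|---|---|
| 1 | 0 | 0.5 | 1.0 | 1 + 0 + 0.5 = 1.5 |
| 1 | −0.25 | 1.0 | 1.0 | 1 − 0.5 + 1.0 = 1.5 |
| 1 | 0.2 | 0.1 | 1.0 | 1 + 0.4 + 0.1 = 1.5 |
| 1 | −0.5 | 1.5 | 1.0 | 1 − 1 + 1.5 = 1.5 |

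The slope variance ranges from 0.1 to 1.5 with no change in what is observed. With t0 = 1, t01 = −0.5 and t1 = 1, both arms show 1.0 (1 − 1 + 1 = 1.0), so real variation in effect leaves no trace.

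**3. Random slope with covariance fixed at zero.** Then t1 = (intervention variance) − (control variance). It can be fitted, with a positive value only if the intervention arm has the larger variance. It is a comparison of between-preschool variance in the two arms. By step 2, equal variances do not imply a constant effect.

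**4. The arm effect.** With preschool as a random intercept, as the protocol has it, the fixed arm effect is estimated from differences between preschools and does not need the interaction.

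**The case against.** **Allocation is inferred.** The correction for clustering concerns only the baseline comparison, and the remark about cluster trials describes experience in the municipality, not this trial's allocation. This stands as a caveat. Even so, a programme built into the preschool curriculum and shaped by each preschool leaves little room for allocating children individually within a preschool.

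**Preschool is a random effect, so something can be estimated.** True with zero covariance, and a comparison of variances by arm may be of interest when each preschool adapts the programme. But that is a different question from the one the words interaction and tested convey. Choosing a parametrisation in the SAP would not change what the data can identify.

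**The primary analysis is spoilt.** A reader might infer this, since with fixed preschool terms the arm effect is itself aliased. The document does not support it: preschool enters as random, and the interaction is an added test.

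**The test should go from all five models.** A reader might infer this too. In the WP 7 Grade 9 model, *school* may mean the later school, where children from both arms could mix and the interaction could be estimated. The text does not say which is meant.

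**Adjustment for area socioeconomic status will be lost.** It is tempting to conclude this, and to attach confidence limits to its random-effect standard deviation. Such limits need a number of levels, which the document does not give, so they would not describe this trial. A random intercept is defensible if the term stands for a grouping with enough areas. WP 1 and WP 6 also add imbalanced covariates, and WP 7 adds household socioeconomic status.

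**Conclusion.** The point holds for both WP 1 models, the WP 6 models and the WP 7 executive-function model, on the strongly implied assumption that whole preschools are allocated. The stated test has no degrees of freedom as fixed terms and is not separately identified as a random slope. With zero covariance it compares between-preschool variances by arm only. The algebra does not depend on the number of preschools.

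The consequence is limited. No bias or loss of power in the primary comparison follows, and the arm effect with a random preschool intercept stands. What is at risk is a misreported finding on heterogeneity, or an avoidable departure from the protocol. It is worth correcting, but it is not a must-fix for the primary estimate.

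For the WP 7 Grade 9 model the conclusion is open until *school* is defined. The treatment of area socioeconomic status is a secondary point that depends on how that variable is defined.

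**What to change.** 1. In both WP 1 models, the WP 6 models and the WP 7 executive-function model, delete the interaction test. If variation between preschools is of interest, replace it with either (a) a comparison of between-preschool variance by arm, labelled as such, or (b) an interaction of arm with a measured preschool-level characteristic such as area socioeconomic status.
2. Keep preschool as a random intercept.
3. In the WP 7 Grade 9 model, state whether *school* is the preschool or the later school. Delete the test there only if it is the preschool.
4. State the unit of randomisation beside the models, so that the reason is visible.
5. Define area socioeconomic status. If it is a measured category or score with few levels, enter it as a fixed covariate.

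Items 1 to 4 are wording only. Item 5, where it applies, costs one or a few between-preschool degrees of freedom. Option 1(b) uses further between-preschool degrees of freedom, according to how the characteristic is coded.
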